#### Sentence generation task.

This is a direct measure of interpretation bias, which has been successfully implemented in previous research from our research group [44,45]. The task included 18 experimental trials featuring nine ambiguous sensory-pain and nine ambiguous neutral stimuli [44]. Trials were presented in a new randomised order for each participant. Each trial began with a fixation cross for 1000ms. A single word replaced the cross, presented in size 40 Times New Roman font which remained on the screen until the end of the trial. Participants read the word and used a keyboard to type a single sentence featuring the word once. Text appeared in size 18 Times New Roman font below the experimental word as the participant typed. Backspace and delete keys were used to correct spelling mistakes or make amendments as necessary, and the F12 key was used submit the response. The next trial began after 120 seconds if no response was submitted. Trials followed one another automatically, with all 18 trials presented in a single block. Two practice trials were initially presented to familiarise participants with the requirements of the task, featuring the words *running* and *dancing*. This task took approximately 15 minutes to complete.

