### Aims and hypotheses

The primary aim of the main experimental study is to investigate the effects of pain-related CBM-I on the interpretation of ambiguous somatosensory stimuli in healthy, pain-free individuals. The secondary aim is to investigate the effects of CBM-I on patterns of pain-related interpretation, attentional and memory bias. A between-groups design will be implemented, randomising healthy participants to benign CBM-I or pain CBM-I conditions. It is hypothesised that:

Participants in the pain modification group will interpret somatosensory stimuli at levels around the pain threshold as more intense and unpleasant than participants in the benign modification group.Participants in the pain modification group will have higher levels of pain-related interpretation bias for ambiguous words and scenarios, as compared to the benign modification group. This is operationalised by:a. In the Ambiguous Scenarios Task, participants in the pain modification group will be more likely to interpret ambiguous scenarios as pain-related, as compared to participants in the benign modification group.b. In the Sentence Generation Task, participants in the pain modification group will generate more pain-related sentences than participants in the benign modification group.Participants in the pain modification group will have higher levels of pain-related attentional and memory biases bias than participants in the benign modification group.

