### Experimental paradigms

Identical to the pilot study, CBM-I training will be achieved via the Ambiguous Scenarios Task [46] modified for pain research by Jones and Sharpe [10]. Assessments of interpretation bias will be made via the test phase of the Ambiguous Scenarios Task and the Sentence Generation task. New to this main experimental study, the probe-position version of the Visual-Probe Task will be used to assess attentional biases for symbolic linguistic stimuli. Specifically, nine sensory-pain and neutral words pairs matched on length and length and Kucera–Francis written frequency [84] will be included (unique to this paradigm and not included in the Sentence Generation Task), which have been validated and used in our former research [62] (Table 4). The task will begin with eight practice trials featuring random letter strings as stimuli. This will be followed by a single block of 64 experimental trials, each of which features one sensory-pain and one neutral word pair. Each trial will begin with a fixation cross in the centre of the screen for 500ms, followed by a randomly selected word-pair presented vertically (i.e., one above the initial fixation cross, the other below) for either 500ms or 1250ms. Immediately after the disappearance of the word-pair, a visual-probe will be randomly displayed in either the upper or lower location replacing one of the former words. Participants must indicate the location of this probe as quickly as possible, using a two-button response-box (with ‘U’ and ‘L’ labels for upper and lower respectively) to provide their response. Following a randomly determined inter-trial interval of either 1000 or 1500 ms, the next trial will begin with the display of the initial fixation cross. The two stimuli presentation times will be applied in a randomised order over all trials. Each of the eight word-pairs will be presented eight times; four times for 500 ms and four times for 1250 ms. Within each exposure duration, each sensory-pain word will appear twice in the upper location and twice in the lower location. The probe location (upper or lower) will be counterbalanced across both locations, resulting in an equal number of congruent (probe replacing the sensory-pain word) and incongruent (probe replacing the neutral word) trials. This task will take approximately 15 minutes to complete. Also new to this main experimental study, a pen and paper version of the free recall task will be used to explore memory biases. Participants will unexpectedly be given two minutes to write down as many words as they can remember from the sentence generation and visual-probe tasks.

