For the Visual-Probe Task, practice and experimental trials with incorrect responses will be excluded from the analyses. Box and whisker plots for overall data will be inspected to identify response time outliers which will be removed. Mean response times for each participant will then be calculated, with any response time three standard deviations above or below this mean also removed as outliers. Attentional bias scores will then be calculated for each participant at each exposure duration (i.e., 500ms and 1250ms) using the following formula:

$$\text{Attentional bias score=}\left(\left(\text{TuPl – TlPl}\right)\text{+}\left(\text{TlPu – TuPu}\right)\right)\text{/2.}$$

Where T =  threatening stimulus, P =  probe, u =  upper position, l =  lower position.

A positive bias score indicates a shift of attention towards the location of threatening words relative to neutral words. A negative bias score indicates a shift of attention away from the location of threatening words towards neutral words [62]. For the free recall memory bias task, the proportion of accurate words recalled per stimuli category will be computed and used in the analyses [44,70,91].

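### The free recall score counts accurate words only, so it cannot separate memory from words participants typed or guessed, and it may lean towards the memory hypothesis

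*Protocol article*

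**What the plan says.** All places are in the Protocol article, mostly in the main-study sections.

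- **Recall task (Experimental paradigms).** "Participants will unexpectedly be given two minutes to write down as many words as they can remember from the sentence generation and visual-probe tasks". This is one pooled sheet, and no record of the source task is described. Under Procedure it comes last among the cognitive bias tasks, before the bias repair task.
- **Scoring (Data reduction and analytic plan).** "the proportion of accurate words recalled per stimuli category will be computed and used in the analyses". The Ambiguous Scenarios and visual-probe scores are each defined as differences; no difference is defined for recall.
- **Hypotheses (Aims and hypotheses).** Hypothesis 2b: "participants in the pain modification group will generate more pain-related sentences than participants in the benign modification group". Hypothesis 3: "Participants in the pain modification group will have higher levels of pain-related attentional and memory biases bias than participants in the benign modification group".
- **Sentence task (pilot methods, retained for the main study).** "The task included 18 experimental trials featuring nine ambiguous sensory-pain and nine ambiguous neutral stimuli". For each cue, "Participants read the word and used a keyboard to type a single sentence featuring the word once".
- **Word lists.** The visual-probe words are described as "unique to this paradigm and not included in the Sentence Generation Task". Table 4 lists eight pain targets, among them *Painful*, *Hurting*, *Aching* and *Sore*.

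**The concern.** The protocol keeps the two presented lists apart, but it cannot keep the participants' own vocabulary apart from Table 4. Someone who typed *painful* in a sentence and later writes it on the recall sheet is credited with remembering the visual-probe list. The same credit goes to someone who guesses a pain word that happens to be listed. A guess is less likely to hit a neutral target such as *Autograph* or *Volley*. An accurate-word count shows neither route.

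The typing route is expected to differ by arm, because Hypothesis 2b predicts more pain-related sentences after pain training. Any error from it runs in the direction of Hypothesis 3. It would also tie the memory score to the Sentence Generation score through shared typed material, and the protocol wants to study how these biases relate.

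A separate, smaller problem concerns the planned correlations. They need one memory score per person, and a raw pain proportion also carries general recall ability.

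**Working it through.** **Sample size.** For a two-group ANOVA with f = 0.244, alpha 0.05 and N = 134, the noncentrality is N × f² = 134 × 0.0595 = 7.98. Power is 0.8006, so the stated 134 reproduces. Equal allocation gives 67 per arm. The planned effect is d = 2f = 0.488.

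**Expected difference in sentences.** Pilot proportions were 0.28 (SD 0.17) and 0.15 (SD 0.10). Over 18 sentences this is 18 × 0.28 = 5.04 against 18 × 0.15 = 2.70, a gap of 2.34 per participant.

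**From sentences to false recall.** The documents give none of the following, so all are assumptions:

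- p: true recall per word, the same in both arms (0.15 to 0.25, varying between people).
- q: chance that a pain-related sentence contains a Table 4 pain word.
- r: chance that a self-typed word is later written down.
- g: extra guess rate per listed pain word, pain arm only.

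Ignoring repeats, the extra accurate pain words are about 2.34 × q × r × (1 − p). With q = 0.25, r = 0.5 and p = 0.15 this is 0.249 words. On a pain list of 9 + 8 = 17 words it is 0.249 / 17 = 0.015. Simulation gives 0.012; it is lower because the same word can be typed twice.

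**Simulation.** There was no true memory difference, with 67 per arm, a two-sided t-test at 0.05 and 2,000 runs per setting. Entries are the percentage of runs significant in favour of Hypothesis 3 (nominal 2.5%). Each pair is p = 0.15 / p = 0.25.

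| Typing only | Pain proportion | Pain minus neutral |
|---|---|---|
| q = 0, r = 0 | 2.7 / 2.2 | 2.6 / 2.4 |
| q = 0.10, r = 0.5 | 5.2 / 4.4 | 3.7 / 4.8 |
| q = 0.25, r = 0.5 | 10.6 / 7.8 | 7.8 / 5.6 |
| q = 0.50, r = 0.5 | 19.2 / 13.6 | 15.6 / 10.2 |
| q = 0.50, r = 0.8 | 36.6 / 24.6 | 29.6 / 20.0 |

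With guessing (p = 0.20, pain minus neutral):

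- Guessing alone: 5.0% at g = 0.01, 9.8% at g = 0.02, 26.2% at g = 0.04.
- Typing plus g = 0.02: 18.0% (q = 0.25, r = 0.5) and 29.6% (q = 0.50, r = 0.5).

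The spurious d ran from about 0.03 to 0.29, below the planned 0.488. A second simulation gave d of about 0.07 to 0.20 and 5 to 18% false support.

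The pain-minus-neutral score lowers the inflation only a little, because neutral recall is untouched by either route.

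**Behaviour of possible corrections.**

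- Dropping self-typed probe words returned typing-only runs to about 2 to 3% when all words were equally easy. When common words were assumed easier, false results *against* Hypothesis 3 rose to 6 to 8%.
- Subtracting intrusions, with a 30% chance that a guess hits a target, gave about 12 to 36% false results against Hypothesis 3.

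**The case against.** Much of the case against a stronger claim is right.

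- **Guessing.** A reader might infer that Hypothesis 2b predicts more guessing of pain words. It concerns sentences only. Extra guessing after pain training is plausible but nowhere stated.
- **Typing.** A reader might infer that the pain arm types more of the target words in general. Both arms type all 18 cue words. A pain-related sentence is defined by its content and need not contain a pain word; the protocol's own example contains no Table 4 word. The route works only through incidental matches to eight targets, at an unknown rate.
- **General recall ability.** A reader might infer that the missing difference score also favours the pain arm. It does not: recall ability has no direction and is balanced in expectation by randomisation. A group-by-category term in a mixed ANOVA would remove it from the group test. Only the correlations are exposed.
- **Size.** Larger figures can be produced. Half an extra word on the eight probe words with an SD of 0.15 gives 0.5 / (8 × 0.15) = 0.42, or 67% false support. That takes the half word as given. It also sets the SD close to the binomial minimum at 20% recall, √(0.2 × 0.8 / 8) = 0.141, which leaves almost no room for differences between people.
- **Scope.** Memory bias is a secondary outcome, and the recording of intrusions may be settled in a fuller plan.

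What remains is that the article does state the score, and that score cannot tell the sources of a written word apart. One of those sources is predicted to differ by arm.

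**Conclusion.** The concern holds in limited form. The stated score cannot separate memory for presented words from words participants typed themselves or guessed, and it may lean towards Hypothesis 3.

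The direction of the typing route rests on Hypothesis 2b and the pilot. The direction of the guessing route is an inference. The size is unknown. Under the assumed rates, false support for Hypothesis 3 is about 5% with weak overlap and 10 to 20% with moderate overlap or overlap plus guessing, against a nominal 2.5%. Only strong overlap or heavier guessing takes it above that.

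The documents do not support saying that a positive memory result would be false. They support saying that, as scored, it could not be attributed to memory alone.

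**What to change.** In the main-study Data reduction and analytic plan:

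1. Keep the accurate-word proportions per category.
2. Define the memory bias score as pain minus neutral recall. Use it for the group test (equivalent to the group-by-category term) and for the correlations, so that general recall ability is removed.
3. Prespecify a sensitivity analysis that drops, from numerator and denominator, any visual-probe word or inflection of it found in that participant's own typed sentences.
4. Count pain and neutral intrusions (written words never presented) blind to group, and report them by arm. Do not subtract them from the score, since that over-corrects.
5. Claim a memory effect under Hypothesis 3 only if it survives the sensitivity analysis and pain intrusions do not explain it.

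The cost is a text search of stored sentences and one more coding pass over the recall sheets, with no new participants, measures or session time. The difference score is slightly noisier. The exclusion in step 3 depends on behaviour after randomisation and may remove easier words from the pain arm, so it belongs in a sensitivity analysis and not in the main test.

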## Discussion

This paper describes a novel protocol for investigating the effect of pain-related CBM-I on the interpretation of ambiguous somatosensory stimuli. Since the proposal of the concept of the zone of uncertainty around experimental pain thresholds in 2019 [12], no paradigm has been developed to explore this concept within the pain-related bias field. To address this gap, we developed the Interpretation of Somatosensory Sensations Assessment (ISSA), which presents stimuli at 60%, 80%, 100%, 120% and 140% of an individual’s thermal pain threshold and collects ratings on pain intensity and unpleasantness. The results of a small pilot study showed this was suitable for use in a full-powered investigation. No ethical concerns were raised in the use of the ISSA by either the participants or the researchers, and the instructions were clear to participants. The app which calculates heat and cold trial temperatures from the individual participant’s pain threshold is publicly available (see URL above) and can be used by other researchers. Although the ISSA is shown to work well for the purposes of our planned investigation, further testing and development of this paradigm is nevertheless encouraged. For example, while we currently use 20% increments above and below the individual pain threshold, different increments (such as 5% or 10%), if detectable, may create varying levels of ambiguity and should be explored in future research. Furthermore, researchers may wish to explore alternative forms of experimental pain induction such as pressure pain administered via automated pressure cuff algometer, which may more closely resemble pain experienced during clinical procedures (i.e., blood pressure readings).

Overall, the intended aims of the pilot study were met, providing important insights allowing us to make modifications to the experimental design in preparation for the main study. Additionally, our research team (e.g., [3,44,45]) and others (e.g., [75,92–94]) are increasingly calling for research exploring the interrelationships between different forms of cognitive bias. The combined cognitive bias hypothesis proposes that different forms of cognitive bias influence and interact with each other, and these interactions may have a greater impact on maintaining emotional disorders than individual biases in isolation [95]. Specifically for pain, the Integrated Contextual-Functional Framework [76] posits that pain-related biases in attention, interpretation, and memory arise from shared contextual and motivational factors. These biases are likely interconnected and may amplify each other. The protocol detailed here will not only allow us to investigate the effects of pain-related CBM-I on the interpretation of ambiguous somatosensory stimuli, but will also allow us to explore the interrelationships between attentional, interpretation and memory biases for symbolic pain-related stimuli. The results of this research with pain-free individuals will likely inform future research on the transition from pain-free states to acute pain, and subsequently to chronic pain in some individuals. Additionally, the novel ISSA paradigm we developed can be used to further explore the zone of uncertainty across other patient populations who may interpret or evaluate ambiguous bodily sensations differently compared to healthy individuals.
